#### Control group: social activity

Participants in the control group will receive monthly sessions regarding physical activity and health-related topics as a complement to standard care. No specific exercise intervention will be conducted for this group. Due to ethical reasons, there will be no limit on co-interventions during the trial. Pharmacological, medical or other types of treatments may be initiated, continued or discontinued independently of research team approval. However, participants who eventually are going to participate in further co-interventions will be signalized, and information on type and duration will be collected and considered as covariates in statistical procedures. Participants are going to be contacted with a regular basis via phone calls to assure retention and motivation.

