	Physical Activity Levels	Accelerometer-based activity monitors *GT9X+ Link* (ActiGraph)	X	

^a^*T0* Baseline, *T1* After 6-month intervention, *T2* 3-month follow-up

The same evaluator will be responsible to perform the same procedures along the three assessment periods, which will be subdivided in five separate moments (Table 2). The exercise professional who is going to provide the MT sessions will not be involved in any data collection.

**Table 2 Tab2:** Schedule for the different primary and secondary and outcomes, screening, and confounder evaluations of each assessment moment per evaluator

*Assessment moments per evaluator*	Prior to Assessment (only at baseline)	1st Cognition & Functionality^**a**^	2nd Cognition, QoL & Physical Fitness^**a**^	3rd Physical Activity Level^**a**^	4th ADL, QoL, BPSD & Caregiver Burden^**a**^	5th Body Composition, Cardiorespiratory Fitness, Hemodynamics & Blood-based Biomarkers^**a**^
***Evaluator 1***	CDR	MMSE TMT	ADAS-Cog QoL-AD patient		QoL-AD caregiver Carer-QoL NPI Barthel Index Lawton & Brody IADL Scale	
***Evaluator 2***		SPPB Handgrip strength	SFT One Leg Balance Test	7-day accelerometer-based monitor		
***Evaluator 3***	Informed Consent and anamnesis (sociodemographic and general clinical data)					VO2 Peak Consumption Anthropometry DXA Body Composition Blood Pressure Arterial Stiffness
***Laboratory***						Blood Analysis

^a^*T0* Baseline, *T1* After 6-month intervention, *T2* 3-month follow-up

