### Confounders

Habitual physical activity levels will be collected before, after the 6-month intervention and at 3-month follow-up using an accelerometry-based method – *ActiGraph GT9X Link* -, for 7 consecutive days [87]. Participants will be instructed to wear the accelerometer attached to an elastic belt at all times except when sleeping, bathing, swimming or other water activities. Data will be collected in 100 Hz epochs and a minimum of 10-h on at least 4 days (1 weekend) will be considered valid data. Physical activity data will be processed using *Actilife* software (*Actigraph LLC* Pensacola, FL) and summarized as time spent in sedentary, light, moderate to vigorous physical activity.

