### Statistical analysis plan

Descriptive statistics will be expressed as mean and standard deviation (SD) or as median and interquartile range (IQR) for continuous variables. Categorical variables will be expressed as frequency and percentages. Normal distribution will be analyzed by the Kolmogorov-Smirnov test with Lilliefors’ (K–S) significance correction and normal probability plots. Statistical comparisons at baseline characteristics will be performed using t-test or Mann–Whitney U-test for continuous variables and Chi-squared test or Fisher’s test for categorical variables.

Age, gender, level of education, dementia type/stage, and other variables will be considered as potential confounders and adjustments will be performed in accordance to detect differences between experimental and control group.

The primary effect parameter will be the difference in the SPPB and ADAS-Cog tests between the experimental and control groups, considering the two different moments of evaluation (baseline and after 6-month of intervention). An analysis of variance (ANOVA) test with repeated measures adjusted for potential confounders will be performed for the intervention-related effects. When a significant F value is obtained, Bonferroni post hoc procedures will be used to evaluate pairwise differences. Additionally, mixed effects models will be performed in order to identify potential predictive factor associated with the changes in primary and secondary outcomes from baseline, post-intervention and over the 3-months detraining period.

A multivariable regression analysis will be performed in order to explore the association between cardiovascular and blood-markers, and cognition.

Statistical analyses will be conducted with the SPSS IBM Statistical Software version 25.0 (SPSS, Inc., Chicago, IL) for Windows with a significance level of *p* < 0.05.

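### Co-interventions during the trial are to be covariates, and follow-up physical activity is classed as a confounder, with no rule limiting adjustment of the primary comparison to baseline values

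*Protocol article*

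**What the plan says.** Three parts of the protocol article bear on this.

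- **Control group: social activity.** For ethical reasons "there will be no limit on co-interventions during the trial". It continues: "Pharmacological, medical or other types of treatments may be initiated, continued or discontinued independently of research team approval". For participants who take up further co-interventions, "information on type and duration will be collected and considered as covariates in statistical procedures".
- **Table 1 and the Confounders section.** Table 1 places accelerometry in a block labelled Confounders, with a footnote giving three time points: T0 (baseline), T1 (6 months) and T2 (3 months after the end). The Confounders section repeats this: "Habitual physical activity levels will be collected before, after the 6-month intervention and at 3-month follow-up".
- **Statistical analysis plan.** After age, gender, education and dementia type/stage, it adds "and other variables will be considered as potential confounders and adjustments will be performed in accordance to detect differences between experimental and control group". For the main analysis, an ANOVA "test with repeated measures adjusted for potential confounders will be performed for the intervention-related effects". No sentence restricts adjustment to values measured before the intervention.

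**The concern.** A variable can confound a group comparison only if it is not itself a consequence of group membership. A treatment begun or stopped during the six months is a post-allocation event, and the duration of one begun during the trial cannot be known at baseline. Activity at T1 and T2 is also measured after allocation. It could plausibly respond to the programme: the Discussion expects participants to stay active once the trial is over, and controls receive sessions on physical activity.

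Conditioning on such a variable does two things. It removes whatever part of the effect passes through the variable. If unmeasured prognosis also drives the variable, it creates an association between group and prognosis that was not there before.

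This matters more here than in a randomised trial. Under Trial design, allocation follows personal availability, so covariate adjustment is the main stated protection for the comparison. Mixing post-allocation variables into the adjustment set weakens that protection for both primary outcomes.

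**Working it through.** **Starting point.** The Sample size section gives a 1-point SPPB difference, SD 2.1, 80% power, alpha 0.05, and 110 participants including 25% dropout. Unadjusted and two-sided:

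n per arm = 2 × (1.96 + 0.8416)² × 2.1² / 1² = 69.2, so 70 per arm, 140 evaluable, and 140 / 0.75 = 187 recruited.

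The stated 110 is reached if ANCOVA is assumed with a baseline–outcome correlation r of about 0.64:

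69.2 × (1 − 0.64²) = 40.9, so 41 per arm, 82 evaluable, and 82 / 0.75 = 110.

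That r is an assumption, because the article does not state it. The point under review does not depend on 110; the figure only fixes what 80% power refers to.

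**Activity, mediation only.** Let m be the share of the effect that runs through T1 activity. The documents give no value, so m is assumed. With the standard error held fixed:

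- adjusted effect = (1 − m) × 1 point
- power = Φ[(1 − m) × (1.96 + 0.8416) − 1.96]

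| m (assumed) | Adjusted effect | Argument of Φ | Power |
|---|---|---|---|
| 0 | 1.0 | 0.842 | 80% |
| 0.2 | 0.8 | 0.281 | 61% |
| 0.3 | 0.7 | 0.001 | 50% |
| 0.5 | 0.5 | −0.559 | 29% |

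**Activity, with shared prognosis.** Suppose the programme raises standardised activity by 0.5, an unmeasured prognostic factor loads 0.3 on activity, and the same factor is worth 1 SPPB point per SD (all assumed). Given group, the spurious slope of SPPB on activity is 0.3 × 1 / 1 = 0.3. Adjustment therefore shifts the group estimate by a further −0.3 × 0.5 = −0.15. A true effect of 1.00 becomes 0.85 with no mediation, 0.60 with 25% mediated and 0.35 with 50% mediated. A true effect of 0 becomes −0.15. A simulation of 400,000 participants gave the same values.

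**Co-interventions.** The same kind of simulation used assumed uptake rates. *Driven by prognosis* means that people with a worse outlook are more likely to start the co-intervention. The true exercise effect is 1 point unless stated otherwise.

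| Uptake, exercise vs control | Value of co-intervention | Driven by prognosis | Estimate without covariate | Estimate with covariate |
|---|---|---|---|---|
| 20% vs 20% | 0.5 | no | 0.99 | 0.99 |
| 20% vs 20% | 0.5 | yes | 1.01 | 1.01 |
| 10% vs 30% | 0 | yes | 1.00 | 0.75 |
| 10% vs 30%, true effect 0 | 0 | yes | −0.01 | −0.25 |
| 10% vs 30% | 0.5 | yes | 0.90 | 0.76 |
| 30% vs 10% | 0.5 | yes | 1.10 | 1.25 |

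With equal uptake the covariate does no harm. With unequal uptake driven by prognosis, the estimate moves down when controls use more and up when the exercise arm uses more.

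**Limit of the check.** In these simulations group was independent of prognosis, so leaving out the post-allocation covariate recovers the total effect by construction. In the actual non-randomised trial, baseline confounding would still have to be dealt with.

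**The case against.** The activity limb is an inference. The analysis section does not mention accelerometry or any T1 or T2 value. The T0/T1/T2 footnote is a visit schedule attached equally to the primary, secondary and confounder blocks. Adjusting for baseline activity alone is compatible with the text, and repeated activity data have a legitimate place in the planned mixed models for predictors of change. This stands: a reader might infer that T1 and T2 activity will enter the primary ANOVA, but the article does not say so. What remains is that activity at all three visits carries the label confounder and that nothing confines adjustment to baseline.

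The co-intervention limb needs no such inference about timing, although the wording is loose and does not name the primary model. Three stronger readings are tempting and should be resisted.

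- **That adjustment must shrink the effect.** The direction depends on which arm uses more and why, and the article gives no reason to expect unequal uptake.
- **That co-interventions are recorded only among controls.** The rule sits under the control-group heading but speaks of participants in general.
- **That such a covariate would then be collinear with group.** A variable that is zero in one arm and varies in the other is correlated with group, not collinear with it.

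The power figures can also be challenged. They concern activity and not co-interventions, rest on assumed mediation shares, and ignore the change in standard error when a covariate related to both group and outcome is added. That is correct, so they are illustrations only.

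**Conclusion.** The point holds in a limited form and should be fixed before analysis. The protocol commits to treating co-interventions during the trial as covariates and leaves the way open for post-baseline activity to be used as a confounder in the primary model. Either can bias the SPPB and ADAS-Cog comparisons. The sign is not fixed, and for co-interventions the bias is small if uptake is similar in both arms.

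The documents give no mediation share, no uptake rates and no link between uptake and prognosis, so the size cannot be derived. Under the assumptions shown, a 1-point SPPB effect could be reported as anything from about 0.35 to 0.9 point after adjusting for activity (0.9 corresponding to 10% mediated and no shared prognosis). Adjusting for co-interventions moved the estimate by about 0.15 to 0.25 point, up or down, when uptake differed by 20 percentage points and followed prognosis. The sample size is unaffected.

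**What to change.** 1. In the Statistical analysis plan, state that the primary SPPB and ADAS-Cog comparisons adjust only for variables measured at T0. Include baseline accelerometer activity and treatments in use at baseline; a non-randomised comparison needs both.
2. In Table 1 and the Confounders section, apply the label confounder to the T0 activity value only. Analyse T1 and T2 activity as an outcome, or in labelled mediation or exploratory analyses.
3. In place of the general covariate rule, state that co-interventions are recorded in the same way in both arms and reported by arm, and that they enter a model only in a labelled sensitivity analysis. The freedom to start or stop treatments is not in question.

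The cost is a change of wording, plus minor extra recording if co-interventions are at present noted only for controls. The Trial status section reports recruitment as still under way, so it should not be assumed that everything needed has already been collected.

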## Outcomes

### Primary outcome

Our primary outcomes are physical and cognitive function. Physical function will be measured using SPPB [51, 52] that assesses balance, gait capacity and lower limb strength. The total score ranges from 0 to 12, with higher scores indicating better function. A 1-point change has been described as a meaningful change in physical performance [42]. Cognitive function will be evaluated using the Portuguese version of the ADAS-Cog [53, 54] which comprises fundamental features of cognitive decline such as memory, praxis, constructive ability, language and orientation. Scores range from 0 to 68, with higher scores suggesting greater severity of cognitive impairment. A 4-point ADAS-Cog change has been described as clinically meaningful [55, 56]. As presented on Table 1, primary and secondary outcomes are going to be measured at baseline, after 6-month of intervention, and 3-month follow-up after the intervention has ended.

### Secondary outcomes

#### Physical fitness

Physical fitness is going to be measured via the Senior Fitness Test (SFT) [57]. The SFT is reliable for assessing physical fitness in older adults (≥ 60 years old) including those with cognitive impairment [58, 59]. The SFT includes lower and upper-body strength (chair-stand and arm curl test, respectively), aerobic endurance (2-min steps test), and agility/dynamic balance (8-foot up-and-go test). Static balance will be measured with the One Leg Balance Test [60, 61] which has been considered a reliable for IwD. Oxygen consumption (VO_2_ peak) will be measured trough an incremental treadmill test using a modified Bruce protocol designed for older individuals, previously tested with participants diagnosed with AD [62, 63] and which reliability at mild stages has been proved [64]. Finally, handgrip strength will be obtained with a Jamar hand-dynamometer [65], commonly used in IwD.

#### Cognitive function

The Mini Mental State Examination (MMSE) [66, 67], a widely used test of cognitive function among older adults will be used and consists of a 30-item instrument (with higher scores indicating better cognitive performance) that is organized in six cognitive domains – orientation, retention, attention and calculation, delayed recall, language, and visuo-constructive ability. Frequently used in this research field, MMSE test results will allow comparisons between different studies. As stated on *Bossers* et al. (2012) systematic review study, the MMSE and ADAS-Cog are the most used outcome measures to evaluate global cognitive functioning in clinical trials with older adults with dementia. In addition, these tests were found to be valid and reliable in patients with different subtypes of dementia (i.e., Alzheimer’s disease, vascular disease and Lewy body disease) from mild to moderate stages [68]. Executive function will be assessed with the Trail Making Test (TMT) [69] part A – attention, visual scanning, speed of eye-hand coordination and information processing; and part B – working memory and the ability to switch between different stimuli. Time and number of errors will be registered. This test is highly related to participants ability to perform instrumental ADL, and has been used in similar studies [70, 71].

#### ADL’s functionality

Participants independence on performing ADL will be assessed with widely used measurements: the Barthel Index [72, 73] to address ten basic daily activities, such as bathing, dressing and using toilet – with total score ranging from 0 to 100; and the Lawton & Brody Instrumental Activities of Daily Living (IADL) scale [74] – total score ranging from 0 to 8 – to address more complex activities, as shopping, food preparation and ability to handle finances. Lower scores indicate higher problems to perform activities, within both instruments.

#### Body composition & antropometrics

Body composition (e.g., body mass, fat-free mass, fat mass, and appendicular skeletal mass index) will be analyzed through DXA (QDR 4500/A, Hologic Explorer, Bedford, USA) – previously used with AD participants [75]. Anthropometric measurements will be taken using standardized protocols. Waist and hip circumference will be assessed at the midpoint between iliac crest and the bottom of the ribcage, and at the widest portion of the buttocks, with the tape parallel to the floor, respectively, using a spring-loaded measuring tape.

#### Quality of life & BPSD

The Quality of Life – Alzheimer’s Disease Scale (QoL-AD) [76] will be used to measure the dementia participants’ quality of life. The questionnaire includes 13 items such as physical health, energy, mood, memory, family, marriage, friends, and ability to do things for fun. The QoL-AD provides the participant and the caregiver reports of the participant’s QoL and is scored on a 4-point Likert-type scale ranging from 1 to 4 (excellent), with total scores ranging between 13 and 52 points. The Neuropsychiatric Inventory [77] will be used to determine the frequency and severity of BPSD with a total score ranging from zero to 144 points with high scores corresponding to worsening of BPSD.

#### Caregivers burden

The Care-related Quality of Life instrument (CarerQol) will be used to address subjective burden (CarerQol-7D), and caregivers’ well-being (CarerQol-VAS), using a visual analogue scale to ask about happiness between 0 and 10 (completely happy) [78, 79]. The subjective burden is measured in seven dimensions: fulfillment, relational problems, mental health, daily activities problems, physical health and support. Total CarerQol-7D score ranges from 0 to 14 points with higher scores indicating better caregiving situation.

### Subsample studies

#### Blood-based biomarkers and hemodynamics

At baseline, after the intervention (6-months) and 3-months after intervention has ended, venous blood samples from the antecubital vein will be taken from a subsample. All the biochemical analysis will be performed in a certified commercial laboratory.

Non-fasting venous blood samples will be collected into serum-separating tubes (serum isolation) or tubes containing EDTA (whole blood or plasma isolation). Traditional plasma biochemical parameters, including triglycerides (TG), total cholesterol (TC), high-density lipoprotein cholesterol (HDL-C) will be enzymatically measured [80]. Low density lipoprotein-cholesterol (LDL-C) will be determined according to the Friedewald formula estimated by subtracting HDL-C and one fifth of the triglyceride value from the total cholesterol level [81]. Whole blood glycated hemoglobin (HbA1c) will be measured using high performance liquid chromatography (HPLC) [82].

Serum levels of C-reactive protein (CRP, high-sensitivity test), intercellular adhesion molecule-1 (sICAM-1), vascular cell adhesion molecule-1 (sVCAM-1), metalloproteinase-9 (MMP-9), interleukin (IL) 10, IL-8, IL-6, brain-derived neurotrophic factor (BDNF) and vascular endothelial growth factor (VEGF) will be evaluated by an enzyme-linked immunosorbent assay (ELISA) using commercially assay kits according to the manufacturer’s instructions (R&D System, Minneapolis, MN, USA). Serum levels of creatinine will be measured using the Jaffé-method [83]. Serum levels of tumor necrosis factor-alfa (TNF-alfa) and insulin like growth factor 1 (IGF-1) will be analyzed by chemiluminescent immunoassay (CLIA) method accordingly to the manufacturer’s protocol (Siemens Immunolite 2000, Munich, Germany).

These blood biomarkers will be included in the project due to current evidence of their involvement with dementia risk factors, such as dyslipidemia, inflammation, and endothelial dysfunction [84]. Additionally, we will evaluate blood biomarkers known to play an important role in the relationship between exercise and brain health, including the growth factors BDNF, IGF-1 and VEGF [85].

The same subsample will be assessed for blood pressure and arterial stiffness. Blood pressure is going to be assessed by a digital sphygmomanometer (Colin, BP 8800, Critikron, Inc., USA) and arterial stiffness is going to be measured as carotid-femoral pulse wave velocity (cfPWV) using applanation tonometry (SphygmoCor, AtCor Medical, Australia). Procedures will follow international guidelines [86]. In brief, sequential and consecutive carotid and femoral pressure waves are going to be registered together with the electrocardiogram, that will serve as a reference to calculate the transit time between the recording’s sites. The distance travelled by the pressure wave will be the direct distance between the recording points at the femoral and carotid arteries, corrected by the factor 0.8 [86]. The value of cfPWV is going to be calculated as the direct distance (in meters) divided by the transit time (in seconds). All measurements will be performed in duplicate by the same trained researcher.

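### The pulse wave velocity formula omits the 0.8 distance correction stated one sentence earlier; LDL-C calculated from non-fasting blood needs at most a label

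*Protocol article*

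**What the plan says.** Both measures are described in the protocol article under Subsample studies, Blood-based biomarkers and hemodynamics. Table 1 lists them as secondary outcomes at baseline (T0), after the 6-month intervention (T1) and at the 3-month follow-up (T2).

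**cfPWV.** The article says that procedures follow international guidelines, then gives a short description. The distance travelled by the pressure wave is the "direct distance between the recording points at the femoral and carotid arteries, corrected by the factor 0.8". The next sentence gives the calculation: "The value of cfPWV is going to be calculated as the direct distance (in meters) divided by the transit time (in seconds"). The factor does not appear there.

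**LDL-C.** "Non-fasting venous blood samples will be collected into serum-separating tubes (serum isolation) or tubes containing EDTA". The lipids measured directly are given as "including triglycerides (TG), total cholesterol (TC), high-density lipoprotein cholesterol (HDL-C) will be enzymatically measured". LDL-C is then derived from them: "determined according to the Friedewald formula estimated by subtracting HDL-C and one fifth of the triglyceride value from the total cholesterol level".

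The Statistical analysis plan section uses these markers in an exploratory multivariable regression relating cardiovascular and blood markers to cognition.

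**The concern.** The cfPWV description uses one term for two quantities. In the first sentence, the direct distance is what is measured before the factor is applied. In the second, the same term is the numerator of the velocity. An analyst who programs the second sentence as printed leaves the correction out; one who works from the first applies it. The article does not say which is intended. At stake are the level of every reported cfPWV value, the size of any group difference in m/s, and whether the results can be set beside values obtained under the guideline that the protocol cites for the correction.

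The LDL-C matter is smaller. The formula contains a triglyceride term and the blood is non-fasting, so the calculated value can move with the last meal even if nothing else changes. Unlike a constant factor, such movement could differ between participants and between visits.

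**Working it through.** The article reports no cfPWV or LDL-C value, so there is no figure of its own to reproduce. The check is direct arithmetic on the printed rules.

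**cfPWV**

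Inputs: direct distance D (m), transit time t (s), and the factor 0.8 from the distance sentence.

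- Distance sentence carried into the velocity: v1 = 0.8 x D / t
- Calculation sentence read literally: v2 = D / t
- Ratio: v2 / v1 = 1 / 0.8 = 1.25 for every D and t

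With assumed values of D and t:

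| D (m) | t (s) | 0.8 x D / t (m/s) | D / t (m/s) |
|---|---|---|---|
| 0.50 | 0.040 | 10.0 | 12.5 |
| 0.50 | 0.050 | 8.0 | 10.0 |
| 0.60 | 0.050 | 9.6 | 12.0 |

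Effect on the analysis if one rule is applied to everyone at every visit:

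- Means, standard deviations and differences in m/s are all multiplied by 1.25.
- Test statistics, p-values, standardised effects and percentage changes do not move, because numerator and denominator scale together.
- A regression coefficient per m/s of cfPWV is multiplied by 1/1.25 = 0.8; its test is unchanged.

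If the rule changed between visits, an unchanged participant would show an apparent change of +25% (corrected to uncorrected, 1.25 - 1) or -20% (the reverse, 0.8 - 1).

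**LDL-C**

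Rule: LDL-C = TC - HDL-C - TG/5. The change after a meal is therefore

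change in LDL-C = change in TC - change in HDL-C - (change in TG)/5.

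If TC and HDL-C are assumed unchanged, this reduces to -(change in TG)/5. The article gives no lipid values, so the following are assumptions: TC 200, HDL-C 50 and fasting TG 120 mg/dL, which give LDL-C = 200 - 50 - 24 = 126 mg/dL.

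| Assumed TG rise (mg/dL) | Calculated LDL-C (mg/dL) | Shift (mg/dL) | Shift (%) |
|---|---|---|---|
| 10 | 124 | -2 | -1.6 |
| 30 | 120 | -6 | -4.8 |
| 50 | 116 | -10 | -7.9 |
| 100 | 106 | -20 | -15.9 |

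If TC instead rose by one fifth of the TG rise, with HDL-C constant, the shift would be zero. The range therefore runs from nothing upward, and the article cannot narrow it. Non-HDL cholesterol, TC - HDL-C, contains no TG term.

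**The case against.** On cfPWV, the fair defence is that the description is openly abbreviated, defers to international guidelines and states the correction. The direct distance in the calculation sentence may simply be shorthand for the distance just defined. That is plausible. A reader might infer that the protocol computes velocity from the uncorrected distance, but the article does not say so. What stands is that the calculation sentence reuses the name of the quantity before correction, so the two sentences give different numbers if each is taken at its word.

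The defence can add that a constant factor changes no hypothesis test, and that the article sets no cfPWV threshold for eligibility or analysis. Both points are correct and limit the consequence to absolute values, m/s differences and external comparison.

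On LDL-C, a reader might infer that the values will be wrong. The article does not support that. It is consistent in stating non-fasting samples and the formula, nothing in it restricts the formula to fasting blood, and the shift depends on TC and HDL-C staying fixed. A reader might also infer bias between arms, since allocation follows personal availability (Trial design). No section indicates that sampling times differ by arm, so this is conjecture. Without such a difference, meal timing adds mainly noise or a shift common to both groups.

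**Conclusion.** The cfPWV sentences conflict and should be reconciled. Read literally, the formula gives 1.25 times the value implied by the distance defined one sentence earlier. This follows from the printed factor alone and rests on no assumption about D or t. The effect is confined to absolute cfPWV, differences in m/s and comparison with values obtained under the cited guideline. Inference within the trial is unaffected provided one rule is used throughout.

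The LDL-C remark is a minor measurement weakness of unknown size, not a demonstrated error, and the figures for it are illustrations under assumed lipid values. Both measures are secondary outcomes in a subsample. The SPPB and ADAS-Cog analyses and the sample size are untouched.

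**What to change.** Replace the calculation sentence by: cfPWV (m/s) = (0.8 x direct carotid-femoral distance in m) / transit time in s, and state that the same rule applies at T0, T1 and T2. If any values have already been derived, confirm which distance was used; the stored distances and transit times allow recalculation. The cost is one phrase and no new measurement.

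Optionally, label LDL-C and triglycerides as non-fasting in tables and reports, and report non-HDL cholesterol (TC minus HDL-C) alongside. Both components are already measured, so this costs one derived variable. Calculated LDL-C can stay as a listed outcome.
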